
**Table 1 table1:** Data supporting implementation of selected interventions aimed at reducing readmissions.

Intervention	In-person outcomes or care standards	Virtual outcomes or care standards	References
Post-discharge follow-up visit	Reduction in 90-day readmissions	Noninferior to traditional home-based post-discharge program in time to first exacerbation	Saxena et al [31] Mínguez Clemente et al [32]
Inhaler teach-to-goal	Reduction in 30-day acute care visits	Noninferior in rates of inhaler misuse	Press et al [33] Press et al [34]
COPD action plan	Standard practice	Faster exacerbation recovery time compared to no action plan	Farias et al [35]
Smoking cessation education	Hospital-based education program increased prevalence of cessation at 12 months	High rates of quit attempts and satisfaction with services received	Fung et al [36] Chase et al [37]
Medication reconciliation	Toolkits available to disseminate best practices	Pilot study was feasible and resulted in a high number of discrepancies recognized	Mueller et al [38] Heyworth et al [39]
Pulmonary rehabilitation	Reduction in 30-day readmissions, increase in one-year readmissions	Reduction in 30-day readmissions	Myers et al [40] Bhatt et al [41]
Remote monitoring	No “in-person” option	Some reduction in COPD-related readmissions Low quality of evidence, no improvement in quality of life or mortality	Janjua et al [42] Nagase et al [43]

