### Statistical Analysis and Power Calculation

This primary analysis will be an intention-to-treat analysis with both unadjusted and adjusted analyses using generalized estimating equations. The primary intention-to-treat analysis will be applied to all enrolled hospitals and their outcomes, regardless of duration of intervention or implementation and actual adherence to the randomization at each site. Two-factor generalized estimating equations with a Poisson or negative distribution will be used to assess the effect of delivery mode (virtual vs in-person) and implementation support strategy (mentoring vs mentoring plus co-design), along with their interaction. Randomization “group 1” (deliver interventions virtually with mentoring plus co-design implementation support) will be compared to the remainder of the groups (Table 1). Covariates will include patient age, gender, and race, among others; hospital region; hospital type (academic vs community); setting (urban vs suburban vs rural); and hospital size. Models will also adjust for the baseline level of the primary outcomes at each individual hospital. Hospitals will be considered as a random intercept in a generalized linear mixed model, while within-hospital associations will be adjusted as clusters in a generalized estimating equation. We will also conduct pairwise comparisons among the four groups. For the primary effectiveness (30-day COPD-specific revisits) and the primary implementation outcome (reach of bundle), we will use 2-factor GEE with binomial distribution. A 2-sided type I error of 1% will be used for primary outcomes to account for multiple testing. Secondary outcomes, including other COPD-specific and all-cause 30-, 60-, and 90-day ED visits, readmissions, and revisits, will use the same methods as described above. These analyses will be exploratory and will not spend type I error of 5%. Time-to-event outcomes will be assessed via survival analysis with Cox proportional hazard regression models and Kaplan-Meier curves with the log-rank test. Tests of interaction to assess for any relationship between the intervention delivery (virtual versus in-person) and implementation support (mentoring only versus mentoring plus co-design) will also be performed. Given the testing of multiple hypotheses, a 2-sided *P* value of 1% will be considered significant. For analyses of secondary outcomes, a *P* value <5% will be considered significant regardless of type I error spending. For binary or count outcomes such as intervention provided (yes or no), the same statistical methods used in the primary analyses will be applied.

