
The sample size required for the trial is a minimum of 16 sites. For the primary effectiveness outcome of 30-day COPD-specific acute health care use, assuming a 30-day acute care revisit difference of 0.24 between virtual and in-person groups and a cluster size of 602, as was seen in pilot data [19,22,57], along with an intraclass correlation of 0.03, a total of 16 clusters and 4628 patients is needed to have 91% power to detect this difference. For the implementation outcomes of bundle reach, using a modified *z* test and assuming a 20% difference between receipt of interventions between arms and 90% power to detect a difference, 15 clusters with 4560 patients are needed. Both of these power calculations are at a 2-sided significance level of 1%.

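### The primary effectiveness power statement does not reproduce: 16 clusters of 602 is 9632 patients, not 4628, and the 91% does not follow for two proportions 0.24 apart

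*Protocol article*

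**What the plan says.** The section Statistical Analysis and Power Calculation sets the minimum at 16 sites. For the primary effectiveness outcome it reasons from inputs given as "assuming a 30-day acute care revisit difference of 0.24 between virtual and in-person groups and a cluster size of 602", attributed to pilot data, and concludes with "an intraclass correlation of 0.03, a total of 16 clusters and 4628 patients is needed to have 91% power". For bundle reach it says that "15 clusters with 4560 patients are needed". Both calculations use a two-sided 1% level.

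The same section assigns the primary effectiveness and implementation outcomes to a binomial model: "we will use 2-factor GEE with binomial distribution". A few sentences earlier it assigns the effects of delivery mode and implementation support to a two-factor GEE with a Poisson or negative (presumably negative binomial) distribution. The Outcomes section defines the primary effectiveness outcome as a composite of ED visits and hospitalizations within 30 days, which can be read either as any event or as a number of events.

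Randomization and Assignment of Interventions gives four arms in equal ratio. With 16 sites, virtual v in-person is then 8 v 8 clusters.

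**The concern.** The sentence gives a cluster size, a number of clusters and a total number of patients, and the first two do not multiply to the third. It also gives a difference of 0.24 with no scale and no pair of rates. On the natural reading for a binomial analysis, 0.24 is a gap of 24 percentage points, which 16 clusters should detect with far more than 91% power.

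The 16-site minimum, and the attrition allowance in Population and Setting, rest on this calculation. The Results section says the primary implementation-phase manuscript is close, so readers will soon use the 91% to judge how informative a null virtual v in-person result is. If the figure describes another outcome or scale, that judgement has no basis.

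**Working it through.** **Inputs from the protocol article:** difference 0.24, cluster size m = 602, ICC 0.03, 16 clusters, 4628 patients, power 91%, two-sided alpha 1%, equal allocation (8 v 8 clusters). **Not given:** the two rates, the scale of the 0.24, the test for this outcome and the variation in cluster size. I scanned the base rate over its whole range and took clusters of equal size unless stated.

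**1. Patient count.**
- 16 × 602 = 9632, and 9632/4628 = 2.1.
- 4628/16 = 289.25 per cluster.
- 4628/602 = 7.7 clusters.
- For comparison, the reach figures imply 4560/15 = 304 per cluster, close to 289 and about half of 602.

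**2. Effective sample size per arm.** Design effect = 1 + (m − 1) × 0.03, and effective n = 8m / design effect.
- m = 289.25: design effect 9.65; 2314/9.65 = 240.
- m = 602: design effect 19.03; 4816/19.03 = 253.

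**3. Trying to reproduce 91% with two proportions 0.24 apart.** Noncentrality = 0.24 / √[(p1(1−p1) + p2(1−p2))/n]. Power is lowest at 0.38 v 0.62, where the summed variance is 0.2356 + 0.2356 = 0.471.

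| Cluster size | Noncentrality | Minimum power, z | Minimum power, t (14 df) |
|---|---|---|---|
| 289.25 | 5.41 | 99.8% (99.7% with pooled variance) | 98.5% |
| 602 | 5.56 | 99.9% (99.8% with pooled variance) | 98.9% |

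Every other pair gives more.

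**4. The reverse calculation.** 91% power by z at two-sided 1% needs a noncentrality of 2.576 + 1.341 = 3.917. The summed variance would have to be (0.24/3.917)² × 240 = 0.90 at m = 289.25, or 0.95 with n = 253. Two proportions cannot exceed 0.25 + 0.25 = 0.50.

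**5. What the 91% does fit.** For Poisson counts the variance equals the mean. Means of 0.33 and 0.57 differ by 0.24 and sum to 0.90. By z this gives 91% at m = 289.25 and 93% at m = 602.

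**6. A standardised reading.** If 0.24 were in standard deviation units, the noncentrality would be 0.24 / √(2/n) = 2.63 (n = 240) or 2.70 (n = 253). Power by z is then 52% or 55%.

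**7. Minimum detectable difference for a binary outcome.** Assumptions: 16 equal clusters (8 v 8), ICC 0.03, 90% power, two-sided 1%, t with 14 df, and an in-person proportion of 20–30% (assumed; the article gives none). Across both cluster sizes, the difference is about 13–16 points if virtual is lower and about 17–19 points if virtual is higher.

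**The case against.** A reader might infer that no 0.24 difference in a binary outcome could ever give 91%. The documents do not support that, because the article leaves enough unstated for several routes to reach it:
- 4628 patients with the design effect for clusters of 602 give 91.4% at 0.24 v 0.48 and 91.0% at 0.25 v 0.49 (pooled z). That corresponds to 7.7 clusters, not 16.
- One virtual arm against one in-person arm (4 v 4, z) gives 90.4% at 0.30 v 0.54 with m = 289 and 91.3% at 0.38 v 0.62 with m = 602. Pairwise comparisons are planned, although the power sentence reads more naturally as all virtual v all in-person.
- With 8 v 8 clusters and a cluster-size coefficient of variation near 1, power is about 91–92% (z) at base rates of 0.30–0.38 with m = 289.

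None of these is stated as the method. The first drops the 16 clusters, the second changes the contrast, and the third adds an input the article does not give. They narrow the claim to 16 equal clusters, 8 v 8, at the stated ICC; they do not reconcile the sentence.

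A reader might also infer that the trial is underpowered. That does not follow either: if 0.24 is an absolute difference in proportions, the stated power is too low. Nor can one say that 91% shrinks because only 16 clusters supply the degrees of freedom, since no test is named for this outcome; the modified z test is mentioned for reach only.

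Finally, the count model is in the text, so a calculation for counts is not out of place in itself. That stands. The difficulty is that the section names two models and does not say which one the power refers to.

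It is also fair that randomization is complete, so a correction cannot change the number of sites.

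**Conclusion.** The point holds in this form. The stated 16 clusters, 602 per cluster and 4628 patients cannot all be true; the product is 2.1 times the stated total, and this needs no assumption. The scale of the 0.24 is missing. For the binomial analysis, with 16 equal clusters split 8 v 8 and an ICC of 0.03, a 0.24 difference in proportions gives at least about 99.8% power by z or 98.5% by t, so 91% does not follow. The figure fits a count of about 0.33 v 0.57 visits per patient, so the calculation may not describe the binomial primary outcome; which one was meant cannot be settled from the article.

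The direction of the error depends on the scale: the power is understated if 0.24 is absolute, and would be about 52–55% if it is standardised. Until this is resolved, the 91% should not be used to interpret a null result. Whether 0.24 is a realistic difference cannot be judged from the documents.

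**What to change.** Restate the calculation for the outcome and model that will be used for the primary analysis, giving:
- one consistent set of number of clusters, cluster size (with its variation) and total patients;
- the two assumed proportions, or the two rates if a count is meant, with the scale of the 0.24;
- the ICC;
- the test, with degrees of freedom based on clusters.

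Baseline use data are complete, so the in-person proportion, the ICC and the variation in cluster size can be taken from them where possible. State in the same section whether the binomial or the count model is primary.

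Alternatively, replace the 0.24 and 91% with the minimum detectable difference at 16 sites, in both directions and with its assumptions. On those in the check above, it is about 13–16 points if virtual is lower and about 17–19 points if virtual is higher; the baseline data should replace the assumed 20–30%.

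The cost is wording and a short calculation, with no added sites or patients. The restated power may come out higher or lower than 91%.

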### Sensitivity Analyses

We will assess the robustness of our findings with per-protocol and as-treated sensitivity analyses. Per protocol analysis is defined as comparing sites that adhered to their randomization for delivering interventions (all in person or all virtual), and as treated is defined as comparing sites regardless of randomization that delivered interventions all in person versus any virtual (hybrid virtual and in person). These will be repeated in each of the 4 arms, including testing for interaction between intervention strategy and implementation approach and among patient subgroups (eg, gender, age, and socioeconomic status) and hospital subgroups (region and hospital size). We will use 2-way generalized linear mixed models with hospitals considered as random intercepts.

## Results

As of August 2025, 21 sites completed the contextual assessments and developed site-specific implementation plans. Publication of the qualitative data from this pre-implementation phase is anticipated in December 2025. Randomization of sites has been performed, and the sites that were randomized to co-design have completed 3 sessions. Baseline use data collection is complete. Use data collection for the implementation year is nearly complete. Use data collection for years 1 and 2 of the post-implementation phase is ongoing. Quantitative data analyses of the baseline and implementation phase reports are nearly complete, with anticipation of submission of the primary implementation phase manuscript in December 2025, pending submission of final implementation-phase data reports. Anticipate manuscript submission for the post-implementation sustainment analyses is anticipated for September 2026. Qualitative data collection for year 1 of the post-implementation phase is complete, and analysis is under way. Qualitative data collection for year 2 is being initiated as of August 2025.

## Discussion

### Principal Findings

The Reduce REVISITS study will use novel integrated implementation science and human-centered design methodology to investigate bundles of effective COPD TOC interventions with the goal of reducing COPD hospital revisits. Using a virtual adaptation of the MIM strategy with or without co-design support, the interventions under study, delivered in person or virtually, will be tested for feasibility and endurance in addition to effectiveness. By specifically studying virtual delivery of these interventions and their implementation, our study evaluates whether this approach improves reach by integrating into the rapidly advancing telehealth landscape and may be optimally translated into practice even when resources are finite. Our study outcomes include both effectiveness and implementation measures to enhance dissemination and broader-scale implementation of COPD TOC programs.

Prior literature has investigated the effectiveness of multilevel interventions in a variety of disease states. Studies targeting the transition from the adolescent to young adult health systems, for instance, are ongoing and are using multimodal approaches to target information gaps among patients, health care providers, and caregivers [58]. Congestive heart failure and COPD readmission care bundles and post-discharge follow-up programs have been evaluated as a group for overall effectiveness with varying results, particularly for the outcomes of readmission and mortality [24,59,60]. However, which elements of these programs are the most effective and can be easily delivered to multiple health systems are current gaps in knowledge that the Reduce REVISITS study will fill.

The post-pandemic era has ushered in a plethora of virtual health care measures aimed at improving quality and decreasing cost [61]. Even before the pandemic, a randomized controlled trial found that a telehealth-based transitions of care program involving patients with multiple chronic diseases increased medication reconciliation and adherence compared to an in-person–based program, although telehealth did not reduce health care use in the form of ED visits or readmissions [62]. Specific to COPD, virtual pulmonary rehabilitation has been found to be comparably effective to in-person therapy, but routine clinical monitoring provided virtually has not been demonstrated to reduce health care use or cost compared to standard of care in-person visits [63,64]. The use of emerging wearable technologies for remote patient monitoring is also being actively investigated in relation to clinical outcomes in patients with congestive heart failure or COPD [65]. Ensuring the effectiveness of these virtual interventions through studies such as the Reduce REVISITS study and others will undoubtedly improve the care of chronically ill hospitalized patients.

While this study aims to find the most effective and scalable approaches to facilitate COPD TOC, it is unlikely that a one-size-fits-all approach exists for this complex, diverse, and comorbid patient population. Thus, we have specifically designed our study across a wide variety of hospital settings to capture as much of this variation as possible. Another potential limitation could be that patients could seek care outside of their previously used health care system, limiting data collection. By randomizing sites, we hope to mitigate this bias. We additionally will evaluate sites via value-based purchasing programs that have complete revisit data when possible.

In summary, TOC programs serve a vital role in the necessary goal of reducing admissions for COPD and other chronic diseases. The Reduce REVISITS study, with its novel methodology, wide scope of tested interventions, and introduction of co-design support, is poised to transform the landscape of multilevel systems-based interventions for this vulnerable patient population.

### Conclusions

The Reduce REVISITS study uses a pragmatic hybrid type II effectiveness-implementation design to evaluate COPD care transition programs delivered across hospital settings. By integrating mentored implementation with human-centered co-design, this work seeks to identify practical and scalable strategies for delivering evidence-based COPD TOC interventions in both virtual and in-person formats. The study will generate needed evidence on how implementation supports influence reach, effectiveness, and long-term sustainment. Findings will help guide hospitals in optimizing COPD care transitions and reducing preventable acute care use in this high-risk patient population.

## Appendix

Multimedia Appendix 1 Peer review report from DIRH - Dissemination and Implementation Research in Health Study Section, Healthcare Delivery and Methodologies Integrated Review Group (National Institutes of Health, USA).

## Abbreviations

ATS: American Thoracic Society
COPD: chronic obstructive pulmonary disease
ED: emergency department
HOMERuN: Hospital Medicine Reengineering Network
HRRP: Hospital Readmission Reduction Program
ICD-10: International Classification of Diseases, Tenth Revision
MIM: mentored implementation model
RCT: randomized controlled trial
REDCap: Research Electronic Data Capture
REVISITS: Respiratory Emergent Visits using Implementation Science Interventions Tailored to Setting
SHM: Society of Hospital Medicine
TOC: transition of care
